#### Revised sample size calculations for nutrition intervention (PACAM)

The study was originally designed to provide PACAM to all eligible individuals between the ages of 65.0 and 67.9 years living within selected clusters and to record all hospital admissions and ambulatory cases of pneumonia occurring in the clusters. During the implementation of the study the Chilean Ministry of Health (MOH) expressed concerns regarding the unpredictable increase in demand for PACAM and potential greater work load for health centre staff. It was therefore agreed that rather than making the nutritional supplement available to all eligible individuals in the selected clusters, a sample would be defined that would enable the detection of the proposed primary outcome regarding pneumonia incidence, (a reduction of 33% in the incidence of pneumonia in the PACAM intervention group relative to the control).

Furthermore, during the initial months of the project the MOH implemented a new model of health insurance, called AUGE, which provides guaranteed timely access to health services for specific diseases. The diagnosis and treatment of ambulatory pneumonia for people over 65 years was included in AUGE which started in June 2005. This health service advance provided a great opportunity to enhance the standardization of diagnosis and treatment of pneumonia which was also of direct benefit to CENEX.

Age-specific figures derived from the first four months of the CENEX study provided significantly lower estimates of the incidence of hospitalised pneumonia and also a lower ratio of ambulatory to hospitalised pneumonia cases than considered in the original sample size calculation. Considering these lower rates of pneumonia in the study populations, the sample size required to detect the proposed size effect on pneumonia incidence was re-examined. The sample size for the primary pneumonia outcome was calculated for a 33% reduction in the 2 year incidence of pneumonia and was based on the following assumptions:

a) There is a constant ratio of 5:1 for health centre to hospitalised cases of pneumonia.

b) The observed incidence rate of hospitalised pneumonia of 5 per 1000 in the 65.0–67.9 year old age group will remain constant throughout the study, (there is seasonal variation which was taken into account calculating the expected yearly incidence of pneumonia).

c) All cases of pneumonia recorded in a given health centre come from that health centre's catchment area (*or *address information available).

d) The intra-cluster coefficient of the rate of pneumonia across the study clusters is 0.001.

In order to detect the proposed effect size with p < 0.05 and 80% power with 10 clusters per arm, 314 person-years of follow-up per cluster are required i.e. 160 participants per cluster over 2 years. This increase from 100 to 160 individuals per cluster was deemed unfeasible as some of the smaller clusters did not have sufficient un-recruited individuals remaining in the required age group. In order to detect the proposed effect size with 14 clusters per arm we require 200 person-years of follow-up per cluster i.e. 100 participants per cluster over 2 years. The revised sample size requirement increased to 100 participants in each of 28 clusters i.e. 2800 participants. The centralised system for registration of pneumonia cases ensured that there will be virtually no loss to follow-up for this outcome.

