### Data collection among additional eight clusters

Following identical recruitment and screening procedure to that undergone by participants in the original 20 clusters, individuals from the additional eight clusters who provide consent to take part in the study will undergo baseline assessment at their local community centre or in their home. Given the late initiation of this additional sample, participants in the additional eight clusters were enrolled for 18 months. Information on incidence of pneumonia will therefore be collected for 18 months of intervention (including two winter seasons); after this, routine clinic information on pneumonia incidence will be collected on study participants for a further 6 months. The following selected data will be collected at baseline:

1. Basic sociodemographic and economic characteristics

2. Self-reported health status: SF36

3. Self-reported medications currently being taken on a daily basis.

4. Self-reported incidence of, and treatment for, pneumonia within the previous 12 months

5. Self-reported smoking and drinking habits

6. Anthropometry: weight, height and hand-grip strength.

7. Blood pressure measurement: two measurements under sitting conditions separated by five minutes, using a sphygmomanometer.

Ambulatory and hospitalized cases of pneumonia among participants in the additional eight clusters will be identified in an identical manner to that described for the original 20 clusters.

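### The revised pneumonia sample size is not reproduced by its printed assumptions: read as yearly rates, they give about 55–63% power for a 33% reduction, not 80%

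*Protocol article*

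**What the plan says.** The section on revised sample size calculations for the nutrition intervention sets the target: "The sample size for the primary pneumonia outcome was calculated for a 33% reduction in the 2 year incidence of pneumonia". Its inputs are:

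- "There is a constant ratio of 5:1 for health centre to hospitalised cases of pneumonia" (assumption a).
- "The observed incidence rate of hospitalised pneumonia of 5 per 1000" in the study age group, taken to stay constant (assumption b). No time unit follows the figure, but the same sentence adds that "there is seasonal variation which was taken into account calculating the expected yearly incidence of pneumonia".
- "The intra-cluster coefficient of the rate of pneumonia across the study clusters is 0.001" (assumption d).

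Two requirements are drawn from these. The first opens "In order to detect the proposed effect size with p < 0.05 and 80% power with 10 clusters per arm" and arrives at 314 person-years per cluster, given as 160 participants over two years. The second is the design adopted: "In order to detect the proposed effect size with 14 clusters per arm we require 200 person-years of follow-up per cluster", that is, 100 participants per cluster and 2800 in all. Virtually no loss to follow-up is expected for this outcome.

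The section on data collection in the added clusters then says that "participants in the additional eight clusters were enrolled for 18 months".

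**The concern.** Pneumonia incidence is the primary outcome for the supplement, and this calculation is the reason eight clusters were added. The inputs are few and printed, so the requirement should be reproducible. On the natural reading of the rate it is not, and the gap is too large to be rounding. The 18-month follow-up also falls short of the person-years that the calculation requires, whatever rate was used.

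If the power is well below 80%, a non-significant result could be taken as evidence against a 33% reduction when the trial had limited ability to detect one. The cost-effectiveness conclusion for the supplement would inherit that misreading.

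**Working it through.** **Inputs.** Assumption declared here: 5 per 1000 is per year. Control rate λ0 = 5 + 5×5 = 30 per 1000 person-years. Intervention rate λ1 = 0.67 × 30 = 20.1 per 1000. Sidedness is not stated; two-sided 5% is taken, with one-sided shown below. ICC 0.001 converts to a between-cluster coefficient of variation k with k² = ICC(1−p)/p. This gives k = 0.125 on the 2-year risk (p = 0.06) and k = 0.180 on the yearly risk (p = 0.03).

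**Cluster-rate formula** (c clusters per arm, y person-years per cluster):

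c = 1 + (1.96 + 0.84)² × [(λ0+λ1)/y + k²(λ0²+λ1²)] / (λ0−λ1)²

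**Attempt to reproduce the plan's figures.** Solving for y at 80% power, with (λ0−λ1)² = 0.0099² = 9.801×10⁻⁵, λ0²+λ1² = 0.001304 and λ0+λ1 = 0.0501:

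| Clusters per arm | Printed | No clustering | k = 0.125 | k = 0.180 |
|---|---|---|---|---|
| 10 | 314 | 446 | 545 | 713 |
| 14 | 200 | 309 | 353 | 417 |

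With the simpler conversion k² = ICC/λ0 (k = 0.183), the 14-cluster figure is 421. Without the formula's added cluster, the no-clustering figures fall to 401 and 287, still above 314 and 200.

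**Power of the adopted design, 14 × 200, two-sided.** Power = Φ(√[13 × 9.801×10⁻⁵ / (0.0501/200 + k² × 0.001304)] − 1.96).

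- k = 0: √(0.0012741/0.0002505) − 1.96 = 0.295, power 62% (65% without the added cluster).
- k = 0.125: √(0.0012741/0.0002709) − 1.96 = 0.209, power 58%.
- k = 0.180: √(0.0012741/0.0002927) − 1.96 = 0.127, power 55%.
- Two rates with design effect 1 + 99 × 0.001 = 1.099 and 2800 person-years per arm: 0.0099/√(0.0501 × 1.099/2800) − 1.96 = 0.273, power 61%.
- Two proportions over two years, 6.0% against 4.02%, 1400 per arm, same design effect: power 63% (67% with no clustering).

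One-sided power with clustering is 67–70% by the cluster-rate formula and up to 74% by the design-effect methods. One-sided with clustering ignored, it is at most 78%. No variant reaches 80%.

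**Rate at which the printed figures would hold.** With k² = 0.001(1−λ0)/λ0, the formula gives 80% at λ0 = 53.6 per 1000 for 10 × 314 and 53.9 per 1000 for 14 × 200. Other ways of applying the ICC give 41–54 per 1000. All exceed 30.

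**Other readings of the time unit.**

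- As a 2-year figure, the control rate is 15 per 1000 person-years and power is about one third (33–35%).
- As a shorter-period figure scaled to about 9 hospitalised cases per 1000 per year (9 × 6 = 54), power is about 80%.
- As a four-month figure simply tripled (15 × 6 = 90 per 1000 per year), power is about 95%.

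**Eighteen-month clusters.** Each supplies 100 × 1.5 = 150 person-years. With four per arm (14 − 10), each arm has 10 × 200 + 4 × 150 = 2600 person-years, a mean of 186 per cluster. Pro rata, cluster-rate power is 55% (k = 0.125) or 52% (k = 0.180).

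**Events and detectable effect on the yearly reading.** Expected cases are 84 + 56 = 140 with full follow-up, or 78 + 52 = 130 with 2600 person-years per arm. The reduction detectable with 80% power is 41–43% at 200 person-years per cluster and 43–44% at 186.

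**The case against.** The strongest reply is that the rate carries no time unit. The figures came from the first four months of the study, and the protocol says seasonality was allowed for in reaching a yearly incidence. So 5 per 1000 may be a raw short-period figure, and the calculation may have used a higher annual rate. That both printed requirements back-solve to nearly the same 54 per 1000 fits a coherent calculation with an unprinted input. This stands as a reason not to call the 80% an arithmetical slip. It does not rescue the text, because neither that annual rate nor any scaling factor is given.

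Two further inferences are tempting but not supported:

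- A reader might infer that the 2-year incidence of 60 per 1000 was used as a yearly rate. The fit is imperfect: at 60 per 1000 the requirements would be about 272 and 177 person-years rather than 314 and 200, and power would be 84%.
- A reader might infer that the lower observed incidence hardly entered the revision. That needs the rate used in the original calculation, which is never printed. Back-solving it gives anything from about 46 to 62 per 1000, depending on the form of the formula and the rounding of the 19% coefficient of variation.

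On follow-up, the protocol says the 18 months include two winters, as do the 24 months. Pneumonia is seasonal, so the pro-rata calculation is an upper bound on the loss. Six further months of routine data are planned in these clusters, but they fall after the intervention period.

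It is also fair that 80% is printed only in the 10-cluster sentence, and that the data analysis section already promises 95% confidence intervals. The 14-cluster sentence has no other power to refer to, and intervals in the report do not correct a power statement in the plan.

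**Conclusion.** The point holds as a statement about the text: the printed assumptions do not yield the printed sample size. If 5 per 1000 is yearly, the adopted design has about 55–63% two-sided power for a 33% reduction, and about 350–420 person-years per cluster would be needed for 80% by the cluster-rate formula. The yearly reading is an assumption, though the natural one: the sentence speaks of yearly incidence and the requirements are in person-years. A 2-year reading makes the shortfall worse. Only an unprinted up-scaling of a shorter-period figure would restore 80%. It cannot be concluded that the trial is certainly underpowered, or how any discrepancy arose.

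The follow-up mismatch does not depend on the rate: eight clusters supply 150 person-years against a requirement of 200. On the yearly reading this brings cluster-rate power to no lower than about 52–55%, and probably less far down because both winters are covered.

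**What to change.** In the revised sample size section:

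- State the annual control rate of all pneumonia used in the calculation, the time unit of the 5 per 1000, any seasonal scaling, the sidedness of the test and the formula.
- Recompute with 20 clusters at 24 months and 8 at 18 months.
- Replace the 80% claim with the power delivered and the reduction detectable with 80% power. On the yearly reading these are about 52–63% across methods and follow-up assumptions, and about 41–44%.
- Add that a non-significant result would not by itself exclude a 33% reduction, and that the confidence interval should be used to judge this.

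The cost is a recalculation, some wording and, unless a higher annual rate is documented, a less favourable stated power. No extra recruitment or design change is proposed.

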### Recruitment

To obtain a study sample of 2800 individuals, it was expected that approximately 5000 individuals would need to be contacted. A conservative estimate of the proportion of potentially eligible individuals who would meet the entry criteria and agree to participate in the study was 50%.

#### Recruitment status

Following the revision of the sampling strategy, recruitment of the study sample proceeded well and by 28th November 2005, 2600 potentially eligible participants had been identified and by 20^th ^December 2005, 2000 individuals had been recruited to CENEX. Individuals from the additional eight health centres began to be recruited on 10^th ^March 2006 and by 2^nd ^June 2006, 800 additional individuals had been recruited to CENEX. Approximately 70% of eligible individuals agreed to participate in the study.

## Data collection

### Baseline data collection in the original 20 clusters

At the baseline visit, participants were interviewed by project field staff in their local community centre. Participants unable to attend their local community centre were interviewed in their homes by project field staff.

The following information has been collected:

1. Socio-demographic and economic characteristics: standardised questionnaire on family membership, education, marital status, household amenities and tasks, work history (paid and voluntary), contact with family members and help given to them, feelings about age, smoking history and alcohol use. These have been collected in order to help characterise the study population and as predictors of current and future health status.

2. Self-reported health status: the short-form 36 health survey (SF-36) [24] which is well validated for use among adults.

3. Depression: the 15-item Geriatric Depression Scale (GDS 15) [25] will be used to assess the affective state of participants. The GDS 15 is quick and easy to administer and has been validated for use in Chile [26].

4. Self-reported presence of the following medically-diagnosed diseases: pneumonia, diabetes, hypertension, coronary heart disease, stroke, heart failure.

5. Self-reported hospitalization within the previous 12 months as a measure of frailty.

6. Self-reported incidence of falls within the previous 6 months and fractures, and 20 year recall of hip and wrist fracture.

7. Self-reported medications currently being taken on a daily basis.

8. Self-reported health service utilization to assess direct and indirect costs borne by participants.

9. Self-reported frequency of consumption of selected food groups.

10. Self-reported attendance at existing physical exercise classes.

All participants will then be given a further appointment to attend a local community centre a few days later where the following information will be collected by project field staff:

1. Anthropometry: weight; height; arm, waist, hip and calf circumferences; triceps skin-fold thickness; knee height; wrist width; hand-grip strength.

2. Blood pressure measurement: two measurements under sitting conditions separated by five minutes, using a sphygmomanometer.

3. Timed up-and-go: the time taken for a participant to rise from a chair without arm supports, walk three meters, turn around and return to sit on the chair, which is a good marker of mobility among older people.

4. 6-minute walk: the maximum distance walked in 6 minutes by a participant, which is a good marker of muscle strength and functional status among older people.

A random sub sample of 120 participants per study arm will be asked for blood samples (10 ml) collected under fasting conditions in the early morning in the participant's home. The samples will be analysed to determine the concentrations of: total/HDL/LDL cholesterol, triglycerides, C-reactive protein, thyroid stimulating hormone, glucose, insulin and other specific screening markers to determine susceptibility to chronic disease.

Ambulatory cases of pneumonia will be identified from health centre records based on the pre-defined AUGE protocol for ambulatory pneumonia diagnosis and treatment [27]. In addition, project field staff will review the registry of all ambulatory admissions to the acute respiratory disease unit in each health centre, and record all prescriptions for antibiotics given to study participants. Hospitalised cases of pneumonia among study participants will be abstracted from computerised Ministry of Health data. Diagnosis of pneumonia or acute respiratory infection is initially made by a health centre or hospital physician blind to whether the participant is enrolled in the CENEX study. The diagnoses are then independently confirmed (or otherwise), via patient records, by two physicians blind to treatment allocation in the CENEX study.

In order to collect standardised information on the incidence of diseases listed as primary and secondary outcome variables, the medical records of all study participants registered in health centres will be reviewed periodically by project field staff. Uptake by study participants of PACAM products from the health centres, and information on attendance of exercise sessions, and any adverse events during the sessions, will be continually recorded by project field staff.

### Data collection at 12 months in original 20 clusters

All study participants will be interviewed by project field staff in their local community centre, or visited in their homes, 12 months after their baseline visit. The following information will be collected:

1. Self-reported health status: SF36 as at baseline.

2. Depression: GDS15 as at baseline.

3. Cognitive health: MMSE as at baseline and clock-drawing test on random sub-sample

4. Self-reported history of incidence of pneumonia, diabetes, hypertension, coronary heart disease, stroke, heart failure in the previous 12 months.

5. Self-reported history of falls and fractures in the previous 12 months.

6. Self-reported health service utilization: as at baseline.

7. Compliance with the interventions: short series of open and closed questions regarding uptake and utilization of the interventions.

8. Anthropometry: selected anthropometric measures as at baseline.

9. Blood pressure measurement: as at baseline.

10. Timed up and go: as at baseline.

### Data collection at 24 months in the original 20 clusters

A final evaluation of all study participants will be carried out after 24 months of intervention. Study participants will be invited to their local community centre, or visited in their homes, and assessed for:

1. Selected socio-demographic characteristics and productive social activity: as at baseline.

2. Depression: GDS15 as at baseline.

3. Self-reported health status: SF36 as at baseline.

4. Cognitive function: as at 12 months.

5. Self-reported presence of medically-diagnosed diseases: as at baseline.

6. Self-reported hospitalization: as at baseline.

7. Self-reported incidence of falls or fractures in the previous 12 months.

8. Self-reported medications currently being taken on a daily basis: as at baseline.

9. Self-reported health service utilization: as at baseline.

10. Compliance with the interventions: as at 12 months.

All participants will then be given an appointment to attend a local community centre where the following information will be collected by project field staff:

1. Anthropometry: as at baseline.

2. Blood pressure measurement: as at baseline.

3. Timed up-and-go: as at baseline.

4. 6 minute walk: as at baseline.

Information on incidence of pneumonia will be collected for 24 months of intervention (including two winter seasons); after this, routine clinic information on pneumonia incidence will be collected on study participants for a further 6 months.

The sub-sample of 120 participants per study arm will be asked for new blood samples collected under fasting conditions, as at baseline.

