### 2. Recruitment of participants

Following the random assignment of the selected health centres to one of the four trial arms, project field staff initiated the recruitment of potential participants living in the health centre catchment areas. Households within the selected catchment areas, randomly sampled from detailed maps of city blocks, were visited by project field staff, and all potentially eligible older people within selected households were identified. Potential participants were aged 65.0–67.9 years at baseline: individuals in this age-group are currently not eligible to receive PACAM.

A team of 20 project field staff initiated the process of randomly sampling houses in the selected clusters on 4th May 2005, and after two months the team had sampled more than 6000 houses and managed to identify 601 potentially eligible individuals. Of these, 351 individuals stated that they were willing to attend a further appointment, the majority of the remainder stated that they had no time (65%) or no interest (35%). Of the 351 individuals expressing an interest, 242 were recruited to the study. The concomitant availability of 2002 census data made it clear that adults aged 65–67.9 were spread thinly and were also unevenly geographically distributed in the selected clusters. It was therefore decided that a new sampling strategy within clusters was required. The revised recruitment strategy was based on the gathered evidence which indicated that 95% of those who had been identified as potentially eligible via the random sampling procedure, were also on health centre registries. It was therefore agreed that the names of older people on registries held in health centres would be used as the basis for recruitment.

Potential participants identified by either of these strategies received, on contact, an information sheet outlining the nature and importance of the study, and were asked for contact details. The information sheet explicitly stated which intervention the potential participant would receive on providing consent to join the study. This method of randomising clusters prior to identifying participants has been shown to result in potential recruitment bias [17], and extra efforts, such as demonstrations by health workers and public meetings at the health centres were made to ensure that acceptance rates in the four study arms were comparable.

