### Primary outcomes for exercise intervention

Walking capacity (distance walked in six minutes) 24 months after initiation of the intervention.

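### The 24-month six-minute walk, the primary exercise outcome, is assigned to the staff role that recruits by arm and logs class attendance, with no masking or separation of duties stated

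*Protocol article*

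**What the plan says.** All references are to the Protocol article.

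- *Primary outcomes for exercise intervention*: "Walking capacity (distance walked in six minutes) 24 months after initiation of the intervention".
- *Baseline data collection in the original 20 clusters* describes the test as "the maximum distance walked in 6 minutes by a participant". Participants are to "attend a local community centre a few days later where the following information will be collected by project field staff".
- *Data collection at 24 months in the original 20 clusters*: participants receive a further appointment at a community centre, where "the following information will be collected by project field staff". The six-minute walk is the fourth item on that list, after anthropometry, blood pressure and timed up-and-go. The compliance questions are the last item of the interview that comes before this appointment.
- *2. Recruitment of participants*: project field staff began recruiting after the health centres had been assigned to arms. "The information sheet explicitly stated which intervention the potential participant would receive on providing consent to join the study". The same role explains at the baseline appointment what taking part involves.
- *Baseline data collection in the original 20 clusters* also says: "information on attendance of exercise sessions, and any adverse events during the sessions, will be continually recorded by project field staff". The same sentence gives this role the recording of supplement uptake.
- Masking is described in two places. Under *Baseline data collection*, the diagnosing physician does not know whether the patient is in the study, and two further physicians, masked to allocation, confirm the diagnosis independently. Under *Data analysis*, the statisticians are masked.
- *Exercise intervention*: the classes are supervised by physical activity instructors, a different role.

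**The concern.** The trial has a primary outcome for each intervention. For pneumonia, the article separates the people who judge the outcome from those who know the allocation. For the walk, it names an assessor role whose other stated duties reveal the allocation.

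The walk is exposed to this because it measures maximum performance. A tester who encourages more in one arm, or handles stops and turns differently when scoring, changes the recorded distance. Participants know their own arm, so the tester is the main point in this measurement where masking is feasible. Timed up-and-go and hand-grip strength share the problem as secondary outcomes.

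A tester effect of this kind is not removed by the usual safeguards:

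- Intention to treat fixes who is compared, not how they are measured.
- Baseline adjustment does not remove an effect that acts at the 24-month test. Only a tester effect identical at both visits would cancel in a change score, and nothing in the article supports assuming that.
- A larger sample narrows the interval around a biased estimate.
- Masked statisticians receive the distances after any effect has occurred.

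**Working it through.** The point turns on who does what, so the main check is to follow one job title, project field staff, through the article.

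| Task | Role named | Section | Does the task reveal the arm? |
|---|---|---|---|
| Recruiting after cluster assignment, with an arm-naming sheet | Project field staff | 2. Recruitment of participants | Yes |
| Explaining what participation involves | Project field staff | 2. Recruitment of participants | Yes |
| Recording supplement uptake and class attendance | Project field staff | Baseline data collection | Yes |
| Supervising classes | Physical activity instructors | Exercise intervention | Yes, but a separate role |
| Six-minute walk at baseline | Project field staff | Baseline data collection | No masking stated |
| Six-minute walk at 24 months | Project field staff | Data collection at 24 months | No masking stated |
| Confirming pneumonia | Two physicians | Baseline data collection | Masked |
| Analysis | Statisticians | Data analysis | Masked |

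1. Three duties that reveal the arm and both walk measurements carry the same job title.
2. The unit of allocation is the health centre, so each cluster has one arm. Knowing the cluster's arm means knowing the participant's arm. Testing takes place in a local community centre.
3. No section separates these duties within the role or says that walk testers are unaware of the cluster's arm.
4. Knowledge of allocation by the tester is therefore the expected result of following the duties as written. It is an inference, since the article does not say it outright.

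**The plan's own figures.** *Original sample size calculations* gives 162 person-years per cluster over 2 years: 162 / 2 = 81 participants. With 20% drop-out, 81 / (1 − 0.20) = 101.25, so 102 against the stated 100, which is close enough. The 81 cannot be rebuilt, because no mean or standard deviation is given. The point does not depend on it.

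**Illustration of sensitivity only; the bias is assumed.** The design has 90% power at two-sided p < 0.05, so the planned effect equals 1.960 + 1.282 = 3.242 standard errors. Suppose there is no true benefit and the tester bias is a fraction f of the planned effect. The chance of a significant result is then Φ(−1.960 + 3.242f) + Φ(−1.960 − 3.242f):

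- f = 0.10: about 6%
- f = 0.25: about 13%
- f = 0.50: about 37%

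The formula gives the same values for a bias in either direction. Working in fractions of the planned effect avoids having to decide whether the stated 13% refers to distance or to change in distance. These figures do not estimate the bias in this trial.

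**The case against.** The strongest reply is that this is a condensed article. Tester rotas, encouragement scripts and masking of physical-test assessors often sit in a fuller protocol or field manual, and their absence here proves little. Some parts of the article were also not in the text read for this point. That would be a sufficient answer if the article were merely silent. It is not: it names the role that measures the walk and gives that role duties that reveal the arm, while it does describe masking for the other primary outcome and for the analysis.

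Three stronger readings are tempting, and the documents do not support them.

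- A reader might infer that the same individuals recruit, log attendance and test in a given cluster. Only the role is shown. The one headcount, a team of 20, describes house sampling in 2005 and not the 24-month round. The 24-month interview and the physical tests are separate appointments, so different staff could already be doing each.
- A reader might infer that the walk is known to be assessed unblinded. The article never says so.
- A reader might infer that the bias inflates the exercise effect by some stated share of the 13% target. The article gives no basis for a size or a direction, and it is ambiguous whether the 13% is relative to distance or to change.

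It is also fair that classes are run by instructors and not by field staff. This lessens the conflict but does not mask the tester.

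**Conclusion.** The point holds in limited form. The article assigns an effort-dependent primary outcome to a role whose other stated duties disclose allocation, in a design with one arm per cluster, and states neither masking nor separation of duties for that measurement. Testers can be expected to know the arm. Any bias that results would bear on the main exercise comparison, 10 clusters with exercise against 10 without, and the planned analysis could not remove it.

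The size and direction of the bias are unknown from the documents. The conclusion rests on two assumptions: that no separation or masking is set out elsewhere, and that staff testing in a cluster will learn its arm. It should be corrected because the outcome is primary and the remedy is modest. It does not show that the exercise result will be wrong.

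**What to change.** For the 24-month round in the original 20 clusters:

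1. Assign existing field staff so that the six-minute walk, timed up-and-go and grip tests in a cluster are done by people who did not recruit there, did not record attendance or supplement collection there, and are not told its arm.
2. Use one fixed script for encouragement and scoring in all arms.
3. Have the compliance interview done by someone other than the tester, which keeps the present two-stage order. The alternative is to move the compliance questions after the tests, which changes that order.
4. Ask participants not to mention classes or supplements during testing.
5. Record for each test whether the tester became aware of the arm.

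The cost is travel and scheduling between clusters and a short test script, with no new visits or outcomes. The article does not give the number of field staff at 24 months, so the rota needs checking. Masking will be imperfect, because participants know their arm and staff within one trial team may know the arms of other clusters. Where rotation is not possible, keep the script and report the walk as assessed without masking. If testers are already separate and masked, a sentence saying so settles the point.
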